### Measurements for the economic evaluation

#### Cost measures

We will use the Dutch Cost Questionnaire “Trimbos Institute and Institute of Medical Technology Questionnaire for Costs Associated with Psychiatric Illness” (TiC-P) [85] adapted for the German health care system. We will include the costs of any type of health care and medicines (direct medical costs), travel expenses and also those for parking (direct non-medical costs), and the costs related to production losses (indirect costs) [86].

### Quality of life

Quality-adjusted life years (QALYs) will be calculated based on the EuroQol (EQ-5D) [87] and the Short Form Health Survey 12 (SF-12) [88]. The EQ-5D is a validated tool for measuring general health-related quality of life. It consists of five items (mobility, self-care, usual activities, pain/discomfort and anxiety/depression), each of which is rated as causing “no problems”, “some problems” or “extreme problems” [89]. Moreover, to generate the QALYs, a visual analogue scale (VAS) ranging from 0 (worst imaginable health state) to 100 (best imaginable health state) is also an integral part of the EQ-5D.

The SF-12 is based on the 36-item Short Form Health Survey (SF-36), a health-related quality-of-life questionnaire [90]. The SF-12 focuses on eight dimensions of health (physical functioning, role-physical, bodily pain, general health, vitality, social functioning, role-emotional and mental health).

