**Measurements for the economic evaluation**					
Trimbos/iMTA questionnaire for costs associated with Psychiatric Illness	**-**	**x**	**-**	**x**	**x**
Quality of life (EuroQol, SF-12)	**-**	**x**	**x**	**x**	**x**

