### Statistical analysis

#### Clinical analysis

The analysis will be performed according to the Consolidated Standards of Reporting Trials (CONSORT) statement regarding eHealth [91]. The data will be analysed on an intention-to-treat (ITT) basis. Group differences in the baseline values of the primary outcome will be compared using t tests to assess whether randomisation was successful. Missing data will be addressed following the recommendations of Little and Rubin [92] and Schafer [93]. We will analyse the CES-D data at two months post-treatment using between-group analyses of covariance (ANCOVAs) on the individual baseline depression scores, adjusting for sex, age and socio-economic status. We will use Cohen’s d to measure the between-group effect size. Cohen’s d will be calculated as the difference between the mean post-test scores of the intervention group and the control group divided by the pooled standard deviation [94]. All of the other secondary outcomes will be analysed in the similar way.

We will also conduct clinical significance change analyses as described by Jacobson and Truax [95,96]. In the first step, we will test whether the changes from pre-test to post-test are statistically reliable and build a reliable change index (RCI). In the second step, we will calculate the clinical significance. Based on the reliable change index, the participants who display a reliable positive change, no change or a reliable deteriorated change will be classified as responders, non-responders or deteriorated, respectively [95].

As secondary analyses, we will also conduct per-protocol (PP) and completers-only analyses.

To show the long-term effect on the primary outcome after 6 months and 12 months, we will use mixed models.

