### Economic evaluation

The economic analysis will be performed from a societal perspective. We will conduct a cost-effectiveness analysis (CEA) and a cost-utility analysis (CUA). Using the incremental cost-effectiveness ratio (ICER), we will show the differences in the costs and benefits between the two groups. The robustness of the ICER will be determined using non-parametric bootstrapping. Furthermore, we will also use bootstrapping to quantify the uncertainty around the ICER, which will be shown on the cost-effectiveness plane [97] and as a cost-effectiveness acceptability curve [98,99]. To perform the CUA, we calculate QALYs from the EQ-5Q and also from the SF-12.

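### The article ties the EQ VAS to generating QALYs in one section and omits it in another, and does not say whether EQ-5D or SF-12 decides the cost-utility question

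*Protocol article*

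**What the plan says.** Two sections of the protocol article deal with QALYs.

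- **Quality of life** (under Measurements for the economic evaluation) opens with the rule: "Quality-adjusted life years (QALYs) will be calculated based on the EuroQol (EQ-5D) [87] and the Short Form Health Survey 12 (SF-12". After describing the five EQ-5D items it continues: "Moreover, to generate the QALYs, a visual analogue scale (VAS) ranging from 0 (worst imaginable health state) to 100 (best imaginable health state", and closes that sentence by saying that the scale belongs to the EQ-5D.
- **Economic evaluation** (under Statistical analysis) says: "To perform the CUA, we calculate QALYs from the EQ-5Q and also from the SF-12". EQ-5Q is evidently a misprint for EQ-5D. The VAS does not appear here.

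Neither section ranks the two instruments. Table 2 has one row, "Quality of life (EuroQol, SF-12", ticked at baseline (T1), 8 weeks (T2), 6 months (T3) and 12 months (T4). The cost questionnaire (TiC-P) is ticked at T1, T3 and T4. For the comparison itself the article says "Using the incremental cost-effectiveness ratio (ICER), we will show the differences in the costs and benefits between the two groups", and then: "The robustness of the ICER will be determined using non-parametric bootstrapping".

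**The concern.** A QALY is time multiplied by a weight, and the weight must equal 0 for dead and 1 for full health. The VAS, with the end points printed in the article, runs from the worst to the best health a person can imagine. Dead has no fixed place on it, and the rating is the patient's own score, not a value attached to the state described by the five items. The only EQ-5D element that the text expressly links to producing QALYs is nevertheless this scale; the five items are described without reference to an index. An analyst who followed that sentence would compute QALYs on the wrong scale.

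The second issue is interpretation. Two instruments give two cost-utility results, and the article does not say which one is the answer if they differ. Cost-effectiveness is one of the two aims in the title, and the Discussion hopes that the findings will encourage health insurers to adopt such programmes. A reader should therefore know in advance which result carries the conclusion.

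**Working it through.** **1. The plan's own figure.** The only computed figure is 130 per group for the CES-D (d = 0.35, two-sided alpha 0.05, 80% power). It reproduces: the normal approximation gives 129 per group and the t-test version 129.1, rounded up to 130; power at 130 is 0.80 to 0.81. The figure is sound. It enters below only as the group size in step 5.

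**2. The two sections side by side.**

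| Source | Quality of life | Economic evaluation |
|---|---|---|
| EQ-5D | QALY source | QALY source (misprinted) |
| SF-12 | QALY source | QALY source |
| EQ VAS | linked to generating QALYs | not mentioned |
| Which one decides | not stated | not stated |

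The sections agree on two sources and differ on the VAS. EQ-5D in the analysis section could mean the index from the five items or the VAS, and the text does not settle which.

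**3. What raw VAS weights would do.** Let V be a rating, D the point on the scale where dead would lie and F the point for full health. A weight with the right anchors is (V − D)/(F − D). The raw weight is V/100. A group difference of Δ points is then Δ/100 instead of Δ/(F − D). The two agree only if F − D = 100, that is, D = 0 and F = 100. The article mentions no rating of dead, so the error cannot be sized. Rescaling would repair the anchors but would still leave a self-rating.

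**4. Two sources without a ranking.** Assumptions: no true QALY effect, normally distributed estimates, correlation between sources of 0.5 to 0.8. The simulated chance that at least one of two sources shows a positive QALY difference is 0.667 at correlation 0.5 and 0.602 at 0.8, against 0.50 for one named source. Both are negative with probability 1 − 0.667 = 0.333 or 1 − 0.602 = 0.398. By symmetry, the signs differ with probability

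- correlation 0.5: 1 − 2 × 0.333 = 0.33
- correlation 0.8: 1 − 2 × 0.398 = 0.20

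If the VAS counted as a third source, the chance of at least one positive difference would be 0.655 to 0.751. On a one-sided 0.025 criterion, the chance that at least one source favours the intervention is 3.9% to 4.5% with two sources and 4.8% to 6.2% with three. The article plans no such test for the cost-utility analysis, so these last figures are a yardstick only.

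**5. What optional baseline adjustment would gain.** Assumptions: 130 per group, no dropout, utility SD 0.15 to 0.30, equal correlation ρ of 0.4 to 0.8 between visits. Trapezoid weights over 0, 8/52, 0.5 and 1 year are w = 0.077, 0.250, 0.423, 0.250, with Σw² = 0.310. Example with SD 0.25 and ρ = 0.6:

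- SE of the baseline difference = 0.25 × √(2/130) = 0.0310
- variance factor v = 0.310 + 0.6 × 0.690 = 0.724; unadjusted SE of the QALY difference = 0.0310 × √0.724 = 0.0264
- share explained by baseline = (0.077 + 0.6 × 0.923)²/0.724 = 0.55; adjusted SE = 0.0264 × √(1 − 0.55) = 0.0177

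Over the whole range the SE falls from 0.014–0.035 to 0.008–0.023, and baseline explains 34% to 77% of the QALY variance.

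**The case against.** **The VAS sentence may only describe the questionnaire.** Its main clause says that the scale is part of the EQ-5D, and the opening words about QALYs are loosely attached. Both the first sentence of that section and the analysis rule name only the EQ-5D and SF-12. This stands to the extent that one cannot say VAS-based QALYs will be used. It does not remove the need to correct a sentence that assigns the VAS that purpose.

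**Both QALY results are announced.** A reader might infer that the favourable version can be picked afterwards. The documents do not support that: leaving out either instrument would be visible, and the analysis is presented through a cost-effectiveness plane and an acceptability curve, not a significance test. What remains is uncertainty about emphasis and about the conclusion when the results differ. An analysis plan that is not shown may already settle the base case and value set. The hypothesis in the Background is also worded around reducing depressive symptoms, and a cost-effectiveness analysis on that outcome does not depend on the QALY source.

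**Baseline adjustment.** A reader might also infer that the economic comparison is unadjusted, since the clinical analysis uses "between-group analyses of covariance (ANCOVAs) on the individual baseline depression scores, adjusting for sex, age and socio-economic status" and the economic section has no counterpart. The text does not say so. The statement that "we will show the differences in the costs and benefits between the two groups" explains what an ICER compares, and an adjusted increment is also a difference between groups. An article commonly leaves the estimator to the full plan. With randomisation, an unadjusted comparison would carry chance imbalance and lose precision; it would not be systematically biased.

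**Conclusion.** The point holds in two parts. First, the Quality of life section links the VAS to generating QALYs while the Economic evaluation section omits it. Taken literally, the sentence yields QALY weights that are not anchored at dead and full health, and that version would be invalid. This is conditional on raw VAS scores actually being used, so the cost-utility analysis as a whole cannot be called invalid. Second, EQ-5D and SF-12 stand level, with no statement of which decides. Under no true effect and an assumed correlation of 0.5 to 0.8, their QALY differences would disagree in sign 20% to 33% of the time.

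No stated figure in the article is wrong. The effect of VAS weighting cannot be quantified from the documents, and the other sizes rest on assumed correlations and SDs. The problem is confined to the cost-utility analysis and does not touch the CES-D result. It should be corrected because the remedy is cheap and cost-effectiveness is a title aim.

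**What to change.** Reconcile the two sections with one rule:

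- Base-case QALYs use EQ-5D index values from one named value set, as the area under the curve from T1 to T4.
- SF-12-based utilities are a sensitivity analysis.
- The EQ VAS is reported descriptively only and does not enter the QALYs.
- Correct the misprint EQ-5Q.

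Optionally, estimate incremental QALYs by regression on arm and T1 utility, and incremental costs by regression on arm and T1 costs, within each bootstrap replicate. This is a gain in precision from data already scheduled at T1, not a repair of a stated error.

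The cost is a few sentences of wording and, for the optional step, a few lines of code. No new data are needed. The choice should be recorded before outcome data are seen by arm.

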### Statistical analysis

#### Clinical analysis

The analysis will be performed according to the Consolidated Standards of Reporting Trials (CONSORT) statement regarding eHealth [91]. The data will be analysed on an intention-to-treat (ITT) basis. Group differences in the baseline values of the primary outcome will be compared using t tests to assess whether randomisation was successful. Missing data will be addressed following the recommendations of Little and Rubin [92] and Schafer [93]. We will analyse the CES-D data at two months post-treatment using between-group analyses of covariance (ANCOVAs) on the individual baseline depression scores, adjusting for sex, age and socio-economic status. We will use Cohen’s d to measure the between-group effect size. Cohen’s d will be calculated as the difference between the mean post-test scores of the intervention group and the control group divided by the pooled standard deviation [94]. All of the other secondary outcomes will be analysed in the similar way.

We will also conduct clinical significance change analyses as described by Jacobson and Truax [95,96]. In the first step, we will test whether the changes from pre-test to post-test are statistically reliable and build a reliable change index (RCI). In the second step, we will calculate the clinical significance. Based on the reliable change index, the participants who display a reliable positive change, no change or a reliable deteriorated change will be classified as responders, non-responders or deteriorated, respectively [95].

As secondary analyses, we will also conduct per-protocol (PP) and completers-only analyses.

To show the long-term effect on the primary outcome after 6 months and 12 months, we will use mixed models.

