### Sample size

Informed by previous studies [25,32], the sample size is based on the expected difference in the primary outcome (CES-D) between the intervention group and the control group at post-test. This sample size provides 80% power to detect a mean difference of d = 0.35 in the effect sizes for the primary outcome (alpha = 0.05, two-tailed test; calculated using Power Analysis and Sample Size Software (PASS 12)). We will need 130 participants per group; hence a total of 260 participants will be included.

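### Cohen's d is defined from unadjusted post-test means while the primary test is a baseline-adjusted ANCOVA; taking d from the ANCOVA would be more precise at no cost

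*Protocol article*

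**What the plan says.** Under Statistical analysis, Clinical analysis, the protocol article analyses the two-month CES-D by "between-group analyses of covariance (ANCOVAs) on the individual baseline depression scores, adjusting for sex, age and socio-economic status". It continues: "We will use Cohen’s d to measure the between-group effect size". The formula that follows is the "difference between the mean post-test scores of the intervention group and the control group divided by the pooled standard deviation". No covariate enters it, and no other between-group effect size is named. The other outcomes are to be handled in a similar way, so the same definition carries over to them.

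The section deals with baseline imbalance in one other place: "Group differences in the baseline values of the primary outcome will be compared using t tests to assess whether randomisation was successful". That comparison has no stated link to how d is calculated.

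Under Sample size, "the sample size is based on the expected difference in the primary outcome (CES-D) between the intervention group and the control group at post-test", and the planning value is d = 0.35 with 130 per group.

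**The concern.** The test and the effect size come from two different estimators. The ANCOVA removes the part of the post-test difference that chance baseline imbalance explains. The difference in post-test means leaves that part in. The reported size of the effect is therefore less precise than the test it accompanies, and in a single trial it can be moved up or down by an imbalance that the plan has already chosen to adjust for.

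What is at stake is the precision of the reported magnitude and its agreement with the primary model. The validity of the primary test is not in question. Because the formula is written out, this concerns something the article fixes, and is not a detail left to a fuller plan.

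**Working it through.** **Inputs.** From the article: 130 per group, 1:1 allocation, planning value d = 0.35, 80% power, two-sided alpha 0.05. Not in the article: the correlation r between baseline and two-month CES-D. It is assumed to lie between 0.3 and 0.6.

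**The plan's own figure.** For an unadjusted comparison of two means, n per group = 2 × (1.960 + 0.842)² / 0.35² = 2 × 7.851 / 0.1225 = 128.2, so 129. The t-test version gives 129.1, so 130. Power at 130 per group is 0.803 (t) or 0.806 (normal). The stated 130 is reproduced, and 0.35 is on the scale of an unadjusted post-test difference.

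**Relation between the two estimators.** In SD units, with equal SDs at baseline and post-test:

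unadjusted difference = ANCOVA-adjusted difference + r × baseline difference.

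The imbalance thus enters d multiplied by r.

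**Size of the imbalance.** The standard error of the baseline difference is √(2/130) = 0.124 SD, with a 95% range of ±1.96 × 0.124 = ±0.243 SD. The standard error of the unadjusted d is also √(2/130) = 0.124.

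**Effect on d.** The SD of the shift is r × 0.124, and its 95% range is ±1.96 times that. The standard error of the adjusted d is 0.124 × √(1 − r²).

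| r (assumed) | SD of shift in d | 95% range of shift | Range as share of 0.35 | SE of adjusted d |
|---|---|---|---|---|
| 0.3 | 0.037 | ±0.073 | 21% | 0.118 |
| 0.4 | 0.050 | ±0.097 | 28% | 0.114 |
| 0.5 | 0.062 | ±0.122 | 35% | 0.107 |
| 0.6 | 0.074 | ±0.146 | 42% | 0.099 |

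As a check, the two components add up to the unadjusted variance. At r = 0.6, 0.099² + 0.074² = 0.0098 + 0.0055 = 0.0153, which agrees with 2/130 = 0.0154 up to rounding.

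**Bias.** In a simulation of 1,000,000 trials per setting, the mean of the unadjusted d was 0.35 when the true value was 0.35. The adjusted difference over the unadjusted SD has the same expected value. The two differ in precision only.

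**Simplifications.** Sex, age and socio-economic status are ignored, as is the small uncertainty from estimating the SD. Complete data are assumed. With fewer participants analysed both standard errors rise, but their ratio √(1 − r²) stays the same.

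**The case against.** The strongest defence is that the stated d is a conventional and legitimate measure. It is unbiased under 1:1 randomisation and sits on the scale on which the trial was sized. Inference rests on the ANCOVA, which already yields an adjusted difference, and nothing prevents its being reported. The gain is also modest. At r = 0.3 the 95% half-width of d falls only from 0.243 to 1.96 × 0.118 = 0.23, and even at r = 0.6 it is still 0.19. Entry requires a CES-D of 23 or more, and restricting the range in this way would tend to lower r, which favours the smaller figures. All of this stands, and it limits the weight of the point. It gives no reason to prefer the noisier estimator, because the adjusted version keeps the same expected value and scale and uses a covariate already in the model.

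A reader might infer four stronger things that the article does not support.

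- **That d is the main result.** The article gives it no such status.
- **That baseline imbalance passes into d in full.** It is reduced by the factor r, so under the assumed range 40% to 70% of it does not carry through.
- **That d can contradict the test.** The article attaches no test or confidence interval to d. If someone added an unadjusted 95% interval, it would disagree with the ANCOVA on significance in 6.9% (r = 0.3) to 15.2% (r = 0.6) of simulated trials at a true d of 0.35. An unadjusted d of opposite sign to a significant ANCOVA occurred in fewer than 0.02% of trials at those settings.
- **That the replication conclusion depends on d.** The Background says the trial will examine whether an earlier trial's findings can be replicated, and cites d = 0.29 for that trial. The hypothesis it states is a significantly lower level of depressed mood, which the ANCOVA tests. No comparison of d values is set as a criterion.

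**Conclusion.** The point holds as a matter of precision and coherence. The article adjusts its primary test for baseline but fixes an effect size that is not adjusted. With 130 per group and r assumed between 0.3 and 0.6, chance imbalance moves d with an SD of 0.04 to 0.07, and the standard error of d is 5% to 25% larger than it needs to be (0.124/0.118 = 1.05; 0.124/0.099 = 1.25). The size depends on r, which the article does not give. The primary test, its error rate and the sample size are untouched, and the stated d is not biased. This is a free improvement and does not correct an invalid analysis.

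**What to change.** Define Cohen's d as the adjusted between-group difference in CES-D at T2 (8 weeks) from the primary ANCOVA, with the same handling of missing data, divided by the unadjusted pooled SD, and report it with a 95% confidence interval. Keep the unadjusted SD as the divisor so that d stays on the scale of the planning value of 0.35.

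Apply the same definition to secondary outcomes that have a baseline value and are measured in both groups at the time analysed. By Table 2, this leaves out measures collected in the intervention group only, such as the negative-effects questionnaire.

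The d from unadjusted post-test means can be kept, labelled as descriptive, for comparison with earlier trials.

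The cost is one sentence in the analysis plan. No extra data are needed and the sample size does not change.

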### Economic evaluation

The economic analysis will be performed from a societal perspective. We will conduct a cost-effectiveness analysis (CEA) and a cost-utility analysis (CUA). Using the incremental cost-effectiveness ratio (ICER), we will show the differences in the costs and benefits between the two groups. The robustness of the ICER will be determined using non-parametric bootstrapping. Furthermore, we will also use bootstrapping to quantify the uncertainty around the ICER, which will be shown on the cost-effectiveness plane [97] and as a cost-effectiveness acceptability curve [98,99]. To perform the CUA, we calculate QALYs from the EQ-5Q and also from the SF-12.

## Discussion

In the present study, we aim to compare a web-based program with mobile phone support and minimal guidance with a control group, receiving psychoeducation only. We expect the depression level of the participants in the intervention group to be significantly lower immediately after the intervention and also after 6 and 12 months compared with the control group. Our planned analyses will enable us to assess whether the outcomes are sustained over time.

Depressive symptoms in people with diabetes have an adverse impact on mental health, quality of life and on medical outcomes such as blood glucose [3-7]. Compared to the comprehensive body of evidence concerning web-based interventions for depression, very little is known about the efficacy of web-based interventions in persons with comorbid (somatic) disorders. This study will contribute to the evaluation of evidence concerning web-based interventions for participants with diabetes and co-morbid depression.

Depression treatments for adults with diabetes produce economic benefits [100]. Until now, there has been no evidence about the cost-effectiveness of web-based treatments for diabetes with comorbid depression. We will conduct CEA und CUA from a societal perspective. If the intervention is cost-effective, these findings may encourage the health care system (including health insurance companies) to integrate those web-based programs into routine diabetes care.

Because adherence to recommendations involving treatment recommendations and lifestyle changes is often a problem with diabetes patients [35], depressive people [36,37] and with participants in web-based interventions [38], we will use two methods to improve the efficacy of the intervention by increasing the number of sessions completed by the intervention group. Firstly, all of the participants can receive daily text message support [61-64]. Secondly, all of the participants who have not logged in to the program seven days after an email reminder will be contacted by their trainer by phone [65]. The trainer will then try to motivate the participant to continue with the intervention. We decided to focus on these two methods; however there are other approaches such as the concept of persuasive technology [101]. It is unknown which methods should be recommended, so further studies should examine which ones are effective concerning web-based interventions.

